## Abstract

**Background:**

Internet-delivered intervention programs are an effective way of changing health behavior in an aging population. The same population has an increasing number of people with cognitive decline or cognitive impairments. Modifiable lifestyle risk factors such as physical activity, nutrition, smoking, alcohol consumption, sleep, and stress all influence the probability of developing neurodegenerative diseases such as Alzheimer’s disease.

**Objective:**

This study aims to answer two questions: (1) Is the use of a self-motivated, complex eHealth intervention effective in changing multiple health behaviors related to cognitive aging in Dutch adults in the work force, especially those aged 40 and over? and (2) Does this health behavior change result in healthier cognitive aging patterns and contribute to preventing or delaying future onset of neurodegenerative syndromes?

**Methods:**

The Brain Aging Monitor study uses a quasi-experimental 2-year pre-posttest design. The Brain Aging Monitor is an online, self-motivated lifestyle intervention program. Recruitment is done both in medium to large organizations and in the Dutch general population over the age of 40. The main outcome measure is the relationship between lifestyle change and cognitive aging. The program uses different strategies and modalities such as Web content, email, online newsletters, and online games to aid its users in behavior change. To build self-regulatory skills, the Brain Aging Monitor offers its users goal-setting activities, skill-building activities, and self-monitoring.

**Results:**

Study results are expected to be published in early 2016.

**Conclusions:**

This study will add to the body of evidence on the effectiveness of eHealth intervention programs with the combined use of state-of-the-art applied games and established behavior change techniques. This will lead to new insights on how to use behavior change techniques and theory in multidimensional lifestyle eHealth research, and how these techniques and theories apply when they are used in a setting where no professional back-end is available.

**Trial Registration:**

Nederlands Trial Register: NTR4144; http://www.trialregister.nl/trialreg/admin/rctview.asp?TC=4144 (Archived by WebCite at http://www.webcitation.org/6cZzwZSg3)

## Introduction

Multiple systematic reviews and meta-analyses have shown that Internet-delivered intervention programs aimed at health behavior change can have a positive impact on their respective populations. These effects range from weight loss in obese men and women to moderating alcohol intake patterns, smoking cessation, and adjusting dietary patterns [1-4]. Computer-tailored health programs are complex, long-term programs that are appropriate for targeting multiple behaviors requiring a change in behavioral habits [3,5]. In contrast to results reported by Portnoy et al who showed that increasing age was a negative predictor of program effectiveness, a systematic review by our group on the effectiveness of eHealth interventions in older populations provides evidence that older age cohorts can be reached with eHealth interventions [6]. Within the next few years, the upcoming cohort of older adults will be adapted to a new electronic environment, in contrast to previous cohorts who often lacked computer experience and had limited Internet access. This would facilitate further use of eHealth tools, also for prevention targets in the elderly. With Internet penetration in the Netherlands reaching 94% of all households among the population aged 45-75, more widespread use of eHealth by the elderly is likely.

We use Bennett et al’s definition for Internet interventions as “systematic treatment/prevention programs, usually addressing one or more determinants of health (frequent health behaviors), delivered largely via the Internet (although not necessarily exclusively Web-based), and interfacing with an end user” [7]. These eHealth interventions are characterized by being highly structured, mostly self-guided, interactive, visually rich, and they may provide tailored messaging based on end-user data [2,8]. Additional benefits of Internet programs are their 24-hour availability, uniformity in data dissemination and collection [2,9], and their heightened reach [5]. An advantage of creating such a completely self-motivated eHealth program, in comparison to an expert-led intervention, is the fact that the reduction in needed external support exponentially increases the reach of Internet interventions. Thus, Internet interventions can reach as many participants as is technically allowed by the hosting servers [10]. Moreover, since most of the cost of Web-delivered health programs are associated with the development stages rather than the implementation stage itself (in comparison to regular face-to-face treatment), even programs with relatively low effectiveness but a very large reach, could significantly impact public health [4].

Lifestyle interventions through the Internet are not new. However, online lifestyle intervention programs with cognitive functioning as a primary outcome measure are not yet widespread. The next section presents a short overview of the relationship between six major modifiable lifestyle factors and cognitive functioning.

Physical activity is associated with a lower risk of Alzheimer’s disease or any type of dementia, and older people with better cardiovascular function, who are more physically active, have decreased chances of cognitive decline [11,12]. Already in 2007, a plea was made for physical activity trials as prevention for cognitive decline [13]. Furthermore, physical inactivity has been calculated to account for approximately 5.3 million premature preventable deaths in 2008, effectively decreasing global life expectancy by 0.7 years [14]. The Internet has proven to be a valid way of changing participants’ physical activity levels [15]. Albeit in modest ways, average significant effect sizes of 0.14 [16], 0.16 [1,4], and 0.17 [1] can mean great benefits on a societal level.

Good physical fitness (positively) and higher body mass index (negatively) are related to academic performance as early as in third and fifth grade [17]. These effects seem to transfer to later life, with high blood pressure and central obesity being negatively related to global cognitive functioning in general and more specifically executive functions, visuomotor skills, and memory [18,19]. Although the exact mechanisms and functions that are affected still need to be established by future research, being overweight appears to provide additional risk for cognitive impairment. A recent review summarizes the positive effects of antioxidants and balanced nutrition on the delay and avoidance of onset of dementia [20].

Smoking is one of the most studied health behaviors, but only recently researchers have started to investigate whether smoking cessation has a positive effect on cognitive functioning. Even though results do not yet appear definitive, most research points towards current smoking as a risk factor for Alzheimer’s and vascular dementia [21]. However, smoking cessation seems to mitigate the effects of smoking in the past, and relative risk of getting neurodegenerative diseases later in life decreases to normal levels [21,22]. Depending on the number of cigarettes a person smokes daily, the risk of various forms of dementia increases by 1.59 up to 2.72 times [23-25]. In addition to an increased risk of getting dementia, smokers generally have a lower level of cognitive functioning while smoking and experience faster decline as they age [26].

Alcohol consumption is not an unequivocal area in comparison with the behaviors discussed above. Low to moderate alcohol consumption may very well have positive effects on brain health, but too much alcohol is harmful to the brain. Cross-sectional studies show that moderate alcohol consumption (up to three units a day) may have beneficial effects on episodic memory, executive functioning, and processing speed of the brain [27-30]. However, these results should be interpreted with care. There are no systematic or controlled-trial intervention studies available that examine the influence of alcohol consumption on cognitive functioning, but earlier research has shown that alcohol consumption higher than three units per day is harmful to the brain and can cause Korsakoff’s syndrome [31]. In addition, it is not clear whether the positive effects on cognition are the direct result of the alcohol consumption itself. It may also be that people who have a lifestyle that includes moderate alcohol consumption also moderate themselves in other lifestyle areas, making them better cognitive agers. Further, a recent meta-analysis of epidemiological studies claimed that a reduction of 17% in alcohol consumption causes a 10% reduction in risk of cardiovascular diseases [32].

In a very elaborate review, Goel et al conclude that both acute and chronic sleep deprivation severely influence cognitive capabilities, starting with a measurable drop in performance on executive functioning tasks after being awake for 16 hours [33]. Among others, sleep deprivation further negatively influences psychomotor speed, learning and memory, and working memory performance, and causes faster performance deterioration on longer tasks [33]. Sleep deprivation by lifestyle choice, whether it is chronic or acute, affects executive functioning as the prefrontal and anterior cingulate cortices and posterior parietal systems are especially susceptible to sleep loss [33].

An increase in psychosocial stress can lead to burnout or depression, which negatively affects a person’s cognitive functioning [34]. Among others, attention, concentration, flexibility, and memory deteriorate with higher amounts of perceived stress [19,35]. Epidemiological research shows a connection between the tendency to experience stress and the risk of mild cognitive impairment and Alzheimer’s disease [36-38]. Also, the speed at which older people experience cognitive decline is correlated with the tendency to experience stress [36].

Managing these modifiable lifestyle factors could serve as a strong protective factor against neurodegenerative syndromes such as dementia. Stimulating health behavior change via the Internet appears feasible, and even the use itself of computers may serve as a protective factor when it comes to dementia [39]. Therefore, we plan to design an online, complex eHealth intervention aiming at lifestyle improvement with cognition as the primary outcome measurement. The research question for the current intervention with the Brain Aging Monitor (BAM) will be twofold: (1) Is the use of a self-motivated, complex eHealth intervention effective in changing multiple health behaviors related to cognitive aging in Dutch adults in the work force, especially those aged 40 and over? and (2) Does this health behavior change result in healthier cognitive aging patterns, thereby possibly preventing or delaying future onset of neurodegenerative syndromes like Alzheimer’s disease?

## Methods

The methodology of this study protocol follows the Standard Protocol Items: Recommendations for Interventional Trials (SPIRIT) guidelines that are specifically developed to provide guidance for researchers to document their study protocol and ensure that no relevant information is missing [40].

### Study Design

For this study, we will use a quasi-experimental longitudinal pre-posttest design, with measurements at baseline and after 12 and 24 months. Only Dutch individuals within the Netherlands will be recruited. The intervention website is programmed in Dutch and as such will not be feasible for implementation outside the Netherlands. Since the Brain Aging Monitor is an eHealth intervention and the Netherlands has an Internet penetration of 94% of all households [41], there is no limit to its potential reach within the Dutch-speaking community. There are no regional restrictions that keep uptake of the intervention pinned to the region of the research institute. Since the entire intervention is based on self-management, contact with the research team is strictly limited to technical support. Considering the fact that the protocol relates to a pragmatic field study that will recruit both at an individual and organizational level, we cannot give an accurate estimate of the number of sites needed to obtain the necessary number of participants. For a sample size calculation, we refer to the description of sample size (Nederlands Trial Register: NTR4144).

### Eligibility Criteria

The intervention will be performed among the general Dutch population and is aimed at delaying and/or slowing down cognitive aging. A recent study by Singh-Manoux et al showed that cognitive decline can be measured as early as 45 years of age [42]. For this reason, participants are eligible for analysis of the primary outcome if they are at least 40 years or older. The upper age limit is a more pragmatic one, since the intervention is aimed at the Dutch workforce and 67 is the official retirement age. Apart from this age criterion, a participant has to have sufficient comprehension of the Dutch language to understand the digital informed consent form (see Multimedia Appendix 1) and should have regular access to an Internet connection. Because the entire intervention takes place outside of the research facility, no strict control or enforcement is possible over other ineligibility criteria such as neurodegenerative disorders, medicine use, or psychiatric symptoms. Therefore, we decided not to use these and other possible exclusion criteria, which also increases overall external validity.

### Health Behavior Change Theory

Using Lustria’s organizing heuristic for strategies in computer-tailored online behavioral interventions, the BAM is an iterative, self-guided customized health program, with expert-led technical support [5]. The BAM uses different modalities such as Web content, email, online newsletters, and online games. To build self-regulatory skills, the BAM deploys goal-setting activities, skill-building activities, self-monitoring, and email reminders. According to a meta-analysis by Webb et al, applying a more extensive use of theory in online lifestyle tools increases overall effect size [4]. Theory can aid intervention designers identify appropriate targets for intervention, select intervention techniques, and it can illuminate which mechanisms of change are effective [43]. How theory is applied in the BAM will be described after the description of the intervention program itself.

### Intervention

The BAM eHealth intervention website is open to anyone who is interested in the relationship between healthy living and brain aging. Figure 1 gives a short overview of the flow of a new participant within the intervention, and Figure 2 shows a screenshot of the BAM homepage. The BAM is a complex intervention [44], using multiple intervention components aimed at multiple health behaviors. As mentioned, the BAM focuses on physical activity, nutrition, smoking, alcohol, sleep, and stress. The BAM has an assessment and feedback system. After registering, validating their email address, and signing a digital informed consent form, new participants fill out seven short questionnaires (ranging from 4-20 questions or statements): one questionnaire for every lifestyle factor and one additional questionnaire on individual characteristics. Full lifestyle questionnaires and their references can be found in Multimedia Appendix 2. The answers to these questionnaires are used to create a personal lifestyle profile for the participant. The participant receives feedback per question using an easy-to-understand visual traffic light (green=conform to the norm, yellow=close to the norm, orange=much room for improvement, red=non-norm compliant) based on the health authority recommendations, behavior-specific feedback on health authority recommendations, and reference values on peer behavior (if possible and/or applicable divided for age and gender). Figure 3 shows a screenshot of the feedback on the nutrition questionnaire. This gives the participant a fast and detailed overview of their current lifestyle status. Also, the answers to the questionnaires tailor the intervention to the participant. For example, non-smokers will not be confronted with information about smoking or the option of setting goals that apply only to smokers.

The use of short self-reporting questionnaires on health behavior is a decision from a time-saving and retention perspective. Using more elaborate questionnaires would allow for better insight in a participant’s behavior but will likely result in higher attrition [45]. Furthermore, more elaborate questionnaires are likely to pose questions that are difficult to answer for an individual. For example, obtaining a meaningful, valid answer on a participant’s consumed dietary fiber (using the Dutch Healthy Diet index [46]) is very difficult. This would require a 24-hour recall process during the initial registering procedure, risking immediate dropout. Therefore, we chose to use simple questionnaires for all lifestyle areas, where every question covers a behavioral trait that directly relates to a goal that can be set later on in the program.

After the questionnaires, the Brain Aging Monitor Cognitive Assessment Battery (BAM-COG) opens up on the game wall and the Goal-Setting Module (GSM) is unlocked. The BAM-COG is an online cognitive assessment battery that has been specifically developed for use in the BAM and has been validated by our group [47]. These games measure working memory, visuospatial short-term memory, episodic recognition memory, and planning. An instructional arrow will direct the participants’ attention to the fact that the games are open for play. After receiving their personal lifestyle overview, participants can start setting monthly, personal-health behavior goals using the GSM. We based the GSM on the Goal Attainment Scaling (GAS) methodology by Kiresuk [48]. Using the GAS triggers participants to be more conscious about their goals because it does not rely on a single digit. Instead, it requires the participant to fill out a complete scale from -2 to 2 (where -2=“I have made minimal progress”, 0=“I have reached my original goal”, and 2=“I have done a lot better than my original goal”). This not only requires more attention from the participant while setting the goal, but it also enables the BAM to give positive feedback on partially accomplished goals instead of a “yes” or “no” answer to the question “did you reach your goal?”.

Every potential goal is accompanied with a set of instructions guiding the participant towards personally relevant and realistic goal setting. It starts with an example GAS scale, a case of a fictive participant, and a step-by-step instruction to complete the goal-setting process. The GAS system is programmed to return a number of restrictions or error messages to the user: (1) if values overlap, (2) if values are in the wrong direction or scrambled, (3) if values exceed the value of 7 days per week, or (4) if the given 0-value is a step back from the value that was answered during the intake questionnaire. When the goal is set, the participant is given reinforcing feedback on making a good first step towards behavior change. After this message, a list of instructions and tips are given that are relevant for that specific goal. This list is open for the participant to choose their preferential working method and go from very basic instructions (eg, “buy fruit” in case of a goal “eat more fruit”) to signing social contracts or using implementation intentions (eg, “if there is no running group in the neighborhood, then I will start my own running group” in case of a goal “start to work out”) [49].

After a participant has decided which instructions and tips to use, the goal gets transferred to the short-term monitoring system (STMS). Here, participants can monitor their own behavior on a day-to-day basis. Inputting their behavior in the STMS, the system automatically graphs a quick overview of how well a participant is doing for that goal on a week-to-week basis. After a month, the STMS asks the participant to what extent the goal is accomplished on their own original GAS scale. For any score specific to that goal, the BAM gives tailored feedback. If a score of -2 or -1 is obtained, the goal is deleted from the participant’s profile and encouragement to try again is given. However, if a score of 0, 1, or 2 is obtained, the goal gets transferred to the long-term monitoring system (LTMS). In the LTMS, a participant gets monthly follow-up questions to monitor if they still are maintaining their initial level of behavior change. With every monthly question that gets answered, the participant is given tailored feedback to acknowledge their success or motivate the participant to maintain their initial behavior change. Multiple goals can be graphed over time giving a personal overview of all acquired and maintained behavior change goals. If multiple goals are set on the same subject, new goals will overwrite old goals so that only the most up-to-date information is shown. Because the BAM does not dictate how many a goals a participant sets and in what order they do this, it implicitly provides the participant with a conceptual choice between simultaneous or sequential goal setting, giving every participant the option to work at their own pace and preference [50-52].

In order not to overload the participant with questionnaires immediately after registering, the personality questionnaires become available to the participant 7 days after registration. These are the Dutch General Self-Efficacy Scale [53], lifestyle factor specific self-efficacy questions [54], the Positive Affect Negative Affect Scale [55], and the Self-Control Scale [56]. These questionnaires are administered to perform secondary analyses to check if the BAM is more effective in certain personality types. No feedback on the personality questionnaires is provided for the participants.

After all baseline data are collected, the tailored knowledge databases, the buddy system, healthy recipes, and blogs on health behavior and cognitive aging become available. The buddy system is a built-in control mechanism the BAM uses to ensure goal safety. A subset of goals that are suitable for this purpose are anonymously sent to another BAM user to be judged by a BAM buddy on its feasibility and safety. A buddy can judge a goal to be “ambitious”, “not ambitious enough”, “just right”, or in the case of losing weight, “this seems unhealthy”. This gives the goal-setter an opportunity to get instant feedback on the feasibility of their goal. Also, it gives the buddy a “look behind the scenes” that may provide feedback on their own goal-setting behavior, as the exact same situation for somebody else may be perceived as harmful whereas this same goal would be deemed applicable to the participant themselves. At the same time that the buddy system becomes available, participants also get access to the knowledge databases that contain up-to-date information on healthy living and the relationship between the different behaviors and brain health. Last, participants get access to weekly blogs on lifestyle, research and brain aging, and healthy recipes. After 365 and 730 days upon completion of the baseline measurement, they will be recruited for 1-year and 2-year follow-up measurements.

No reasons for discontinuation of the study of a participant by the research team have been specified. There is no disease load that can be exacerbated by participating in the BAM nor is there any medication prescribed that could have negative health consequences. Participants are provided with the option of unsubscribing to the study at any given time in their personal profile space. When a participant decides to leave the program, a short questionnaire is automatically presented to collect data on the reason for unsubscribing and to inquire if the participant may be approached to partake in the 1-year and 2-year measurement, regardless of subscription status. All of this is voluntary and participants can always choose to skip this questionnaire.

Keeping participants engaged with eHealth intervention programs has been a major problem since the field originated [7,57,58]. Several adherence-enhancing strategies are in place with the BAM. First, we upload weekly news updates on the homepage regarding health behavior and brain aging from the largest Dutch news websites. Second, on the dashboard of the participant we will upload weekly blogs and healthy recipes so that the content, apart from user input, changes on a weekly basis. Blogs discuss current topics in research on anything BAM-related in an easy accessible form. Recipes use fresh and healthy products and provide participants with ideas to prepare a healthy meal. Third, a personalized email reminder system is built into the BAM that can be adjusted to the participants’ individual needs. In their personal profile space, a participant can choose to receive daily, weekly, biweekly, or monthly email reminders. These reminders give an overview of current active goals and will link the participant directly to this goal after logging in. Fourth, during the registration process new participants can opt in to receive BAM newsletters, which will be sent using the MailChimp engine. At any time, participants can opt in or opt out of the newsletter. Last, participants get a personal profile space with a quick and easy overview of their current lifestyle. They can make adaptations to their lifestyle, see the results of their goals, and can adjust their settings.

Considering the field setting for this intervention, it is difficult to control for concomitant care, or better yet if the BAM inspires participants to make use of other platforms to alter their health behavior in a positive way, this accomplishes the BAM’s goals. The BAM can and may function as a gateway to healthy behavior. Using the GSM and the yearly follow-up, the BAM can track changes over time even if participants actively use outside help that the BAM refers them to.

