### Research Questions and Outcome Measures

Our primary research questions are the following: (1) Is successful health behavior change related to better cognitive aging patterns over time? Change scores will be calculated by subtracting baseline scores from scores at year 1 and year 2, (2) Does the BAM facilitate health behavior change? (see Multimedia Appendix 3 for the construction of the overall lifestyle score), and (3) Does the BAM facilitate health behavior change in certain specific lifestyle areas better than others?

Our secondary research questions are as follows: (1) Is there a dose-response relationship between the number of goals participants set and the expected amount of health behavior improvement? and (2) Does the BAM increase feelings of self-efficacy in health-related behavior and a change in self-control scores from baseline to 1 and 2 years of intervention, as measured with the Self-Control Scale [56]. In other words, does the BAM increase feelings of being in control of one’s life?

Our primary outcome measures are (1) cognitive change over time, (2) overall lifestyle change over time, and (3) specific lifestyle changes over time. The secondary outcome measures consist of (1) number of goals set, (2) change in self-efficacy, and (3) change in self-control.

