### Participant Timeline

The timeline for the BAM is straightforward (see Figure 1). Participants need to register only once. Immediately after registering, email validation, and the informed consent form, the lifestyle questionnaires are available. Once the lifestyle questionnaires have been completed, the BAM-COG becomes available. Seven days after subscription, the personality questionnaires appear in the personal dashboard. These features are all presented again to the participant 365 and 730 days after their baseline completion. The GSM, STMS, and LTMS are continuous processes from the moment they first become available to the participant. After 1 year (365 days), the data will be collected for preliminary secondary outcome analysis. After the 2-year follow-up (730 days), the data will be used for analysis of both primary and secondary outcomes. The nature of the grant requires that the intervention remain online even after data collection is finished for the initial study period and that the BAM remain open to the public after the study is completed. Adaptations to the program can be made at this time, according to study outcomes.

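### The games that measure the primary cognitive outcome appear also to be program content, and the plan cannot separate retest gain from cognitive change

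*Protocol article*

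**What the plan says.** **Role of the games.** The abstract's Methods paragraph lists "modalities such as Web content, email, online newsletters, and online games to aid its users in behavior change". The section Health Behavior Change Theory says much the same: "The BAM uses different modalities such as Web content, email, online newsletters, and online games". The Intervention section describes the BAM-COG as a cognitive assessment battery: "These games measure working memory, visuospatial short-term memory, episodic recognition memory, and planning". No other games are described anywhere. Data Collection Methods names the BAM-COG as the means of measuring cognition, and Research Questions and Outcome Measures puts cognitive change first among the primary outcomes.

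**Access.** In the Intervention section the battery opens on the game wall once the questionnaires are done, and an arrow draws attention "to the fact that the games are open for play". Participant Timeline adds that "These features are all presented again to the participant 365 and 730 days after their baseline completion". It then says: "The GSM, STMS, and LTMS are continuous processes from the moment they first become available to the participant". The BAM-COG is not in that last list.

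**Analysis.** "Change scores will be calculated by subtracting baseline scores from scores at year 1 and year 2". The section on sequence generation and blinding states that there is no control group. Statistical Analyses makes the primary analyses unadjusted. Where adjustment is considered, the confounders it gives as examples are baseline demographic and behavioral characteristics.

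**The concern.** People who repeat a cognitive test may score higher because they know the test. In this plan such a gain goes straight into the primary outcome: the change score is follow-up minus baseline, and no untreated group sits the same battery to show how much of the change is familiarity. Mean change at 1 and 2 years may then look like healthier aging, or real decline may be masked.

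A second problem arises if the games can be played outside the scheduled sittings. More engaged users might both play more and report more lifestyle change. Practice would then be linked to the exposure in the first primary question, and an association between lifestyle change and cognition could appear with no causal or biological link behind it. Adjustment for baseline characteristics would not remove this, because the extra practice accrues after baseline.

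**Working it through.** **Step 1: what the text fixes about access.**
- Intervention: the games open at onboarding. No closing rule, cap on attempts or choice of scored attempt is given.
- Participant Timeline: the features come back at days 365 and 730, and only the goal-setting and two monitoring modules are called continuous.
- Data Collection Methods: the annual follow-up measurement becomes available on the dashboard.

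The last two point to timed access, but neither says that access ends in between. The question is left open.

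**Step 2: the plan's own figure.** Sample Size gives n=166 and a target of 200 (166 × 1.2 = 199.2). The calculation concerns a reduction in risk factors, not cognition, and this point does not depend on it. I use n=166 only as a realistic analysed number.

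**Step 3: retest gain and mean change.** Assume no true change and a mean practice gain of d, in SD units of the change score. The document gives no value for d, so a range is shown. The probability of a significant gain, two-sided at 0.05, is about Φ(d√n − 1.96), with √166 = 12.88.

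| d (assumed) | d√166 − 1.96 | Probability |
|---|---|---|
| 0.10 | −0.67 | 0.25 |
| 0.20 | 0.62 | 0.73 |
| 0.30 | 1.91 | 0.97 |

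This needs only the scheduled sittings.

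**Step 4: play and the lifestyle-cognition association.** Let amount of play correlate a with lifestyle change and b with change in game score, with no other link between the two. The induced correlation is a × b. Both inputs are assumptions. Rejection rates at 0.05 come from 4,000 simulated trials of n=166.

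| a | b | Induced r = a × b | Rejected |
|---|---|---|---|
| 0 | 0 to 0.5 | 0 | about 5% |
| 0.2 | 0.2 | 0.04 | 8% |
| 0.3 | 0.3 | 0.09 | 22% |
| 0.3 | 0.5 | 0.15 | 49% |
| 0.5 | 0.5 | 0.25 | 90% |

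The first row is the case in which practice is unrelated to lifestyle change. It moves the mean and creates no association.

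**The case against.** A reader might infer that the games stay open throughout the two years and that practice therefore produces the lifestyle-cognition association. The documents do not support that. The sentence about the games being open describes one onboarding step. Participant Timeline has the features presented again at fixed days and does not count the BAM-COG among the continuous processes. The Intervention section treats completion of the baseline measurement as a discrete event. The spurious association needs two things that the article neither states nor excludes: play outside the sittings, and play that varies with lifestyle change. At weak correlations (0.2/0.2) the false-positive rate is close to nominal.

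Three further objections have weight:
- The article never says in so many words that the listed online games are the BAM-COG, and its account of behavior change techniques gives games no role. The Discussion's remark on a motivational edge compares games with standard testing and does not promote repeat play. Still, no other games are described. The Discussion speaks of enhancing the program with applied games that can measure cognition, and the Conclusion pairs applied games with behavior change techniques. The identification is a strong inference, not a stated fact.
- Rules on attempts and scoring may sit in a full protocol or analysis plan, and the flowchart and the validation study of the battery cannot be seen. Their absence from the article is not in itself a fault. But whether the site locks the games or counts plays is a build decision: an analysis plan cannot recover plays that were never logged.
- The abstract names the lifestyle-cognition relationship as the main outcome, and a uniform retest gain does not bias that. It does bias mean cognitive change, which is listed as a primary outcome.

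None of this touches the point about mean change. The Discussion defends the uncontrolled design but does not mention practice.

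**Conclusion.** The point holds in two parts of unequal strength.

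1. **Mean cognitive change.** With a raw, unadjusted change score and no comparator, retest gain cannot be separated from true change, even if the battery is taken only three times. This follows from the design as described. Its size is unknown; for assumed gains of 0.1 to 0.3 SD of the change score, the chance of a significant but empty improvement at n=166 runs from 0.25 to 0.97.
2. **Lifestyle-cognition association.** Inflation is possible but conditional on unscheduled play that tracks engagement. The range of 8% to 90% false positives rests wholly on assumed correlations of 0.2 to 0.5, and the rate stays at about 5% if play is unrelated to lifestyle change.

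The Intervention and Participant Timeline sections leave access between measurement points unresolved and should be reconciled.

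**What to change.** - In Intervention and Participant Timeline, state that the BAM-COG is open only in the baseline, 365-day and 730-day windows, and that the first completed attempt at each game in each window is scored.
- Have the website log the number of plays per game. If any play outside the windows is possible, report a sensitivity analysis of the lifestyle-cognition model by play count. Keep play count out of the primary model: it is a post-baseline variable that may itself reflect cognition or engagement, so conditioning on it can introduce bias.
- State that mean BAM-COG change includes retest gain and will not be interpreted as an intervention effect or as healthier aging.

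The cost is a lock and a counter on a website whose data collection is already automated, one sensitivity analysis and a few sentences. The downside is slightly less engagement if the games would otherwise have been open. Locking and logging limit the second problem; they do not remove retest gain from the scheduled sittings, which is why the limit on interpretation is needed as well.
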